# Jiao-tai-wan for insomnia symptoms caused by the disharmony of the heart and kidney: a study protocol for a randomized, double-blind, placebo-controlled trial

**DOI:** 10.1186/s13063-020-04299-x

**Published:** 2020-05-15

**Keywords:** Jiao-tai-wan, Insomnia, Traditional herbal medicine, Randomized controlled trial, Study protocol, Pattern identification

## Abstract

**Background:**

Insomnia seriously affects people’s normal lives and work. However, effective treatment strategies are scarce. The purpose of this study is to explore the efficacy and safety of Jiao-tai-wan (JTW) for ameliorating insomnia symptoms caused by disharmony of the heart and kidney.

**Design:**

This is a randomized, double-blind, placebo-controlled pilot clinical trial. A total of 124 participants suffering from insomnia symptoms will be randomly assigned to the JTW or placebo group in an equal ratio. The participants will be asked to take JTW or placebo granules twice a day for 1 week. All data will be gathered at baseline and at the end of the drug intervention. The primary outcome measures will be the mean change in the Pittsburgh Sleep Quality Index (PSQI) from baseline to the end of the drug intervention. Secondary outcome measures will include the altered sleep parameters in polysomnography, ^1^H-magnetic resonance spectroscopy (^1^H-MRS) evaluation, the Disharmony of Heart and Kidney Scoring System score, and blood tests, including the levels of serum adenosine and melatonin. A laboratory test will be taken before and after treatment to assess the safety of JTW.

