##### Pittsburgh Sleep Quality Index

The PSQI will be used at the baseline and the end of the drug intervention. The PSQI version used in this study is a 19-item self-reported retrospective questionnaire to access the quality of sleep in the past 7 days, and it is designed to measure seven domains called component scores: subjective sleep quality; sleep latency; sleep duration; habitual sleep efficiency; sleep disturbances; use of sleep medications; and daytime dysfunction [16, 17]. Component scores range from 0 (no difficulty) to 3 points (severe difficulty), and when summed, produce a global score in the range of 0–21. A higher score denotes worse sleep. These syndromes are categorized as mild (0–1), moderate (2–7), or severe (≥ 8) [18]. Then, the scores the participants obtained at baseline will be recorded as score 0, and the scores obtained at the end of drug intervention will be recorded as score 1. The recorder will calculate the reduction rate (RR) according to the following formula: RR = (score 1–score 0)/score 0*100%. Finally, we will assess the clinical curative effect of every participant based on the results of the RR. RR values > 75% will be regarded as a clinical cure, RR values between 50%–75% will be considered as a clinical effective, RR values between 25%–50% will be recognized as a clinical success, and RR values < 25% will be considered ineffective. The primary outcome is defined to have a value of 0 if RR is < 25% (ineffective) and 1 if RR is > 25% (clinical cure, clinically effective, or clinical success). The proportion of 1s (i.e. RR ≥ 25%) will be compared between the treatment and placebo groups.

In addition, Liu et al. [18] presented their opinion that the PSQI is suitable for Chinese patients after they conducted reliability and validity tests [19].

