### Sample size

The ratio of cases between the JTW group and the placebo group is set to 1:1; this study is designed to achieve a statistical power of 80% (two-sided type-1 error of *α* = 5%, *β* = 20%). Based on previous clinical practice [33, 34], we assume a treatment success rate of 40% in the placebo group and 70% in the JTW group over 7 days. The sample size is calculated using the following formula:
$$ N={\left[{\Phi}^{-1}\left(\alpha \right)+{\Phi}^{-1}\left(\beta /2\right)\right]}^2\times \left({\pi}_e+{\pi}_0\right)\left(100-\left({\pi}_e+{\pi}_0\right)/2\right)/{\left({\pi}_e-{\pi}_0\right)}^2 $$where Φ is the cumulative distribution function of the standard normal distribution, and *π*_*e*_ and *π*_0_ are the success rate in the experimental and control groups, respectively. Considering a 20% drop-out rate, a sample size of *N* = 49/(1–0.2) = 62 is needed for each group.

Thus, under the assumptions of a success rate of 70% for treatment and 40% for placebo, and a non-compliance rate of 20%, the sample size required to have at least 80% power of detecting a difference between the two groups at a two-sided alpha level of 5% is 124 participants.

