### Statistical analysis

We will use two-sided *p* values for the primary outcome and for all secondary outcomes and safety variables. For the primary outcome, we will use Fisher’s exact test to test the hypothesis at null: the treatment has the same efficacy as the placebo. For each secondary outcome, defined as the value difference between baseline and end-of-intervention, we will use the following tests: (1) t-test for the continuous PSG variables; Chi-square test for the categorical PSG variables; (2) t-test for the blood-level adenosine and melatonin; (3) t-test for the GABA/Cr ratio; and (4) Wilcoxon rank sum test for the Disharmony Score of Heart and Kidney. For safety evaluation of JTW, a two-sided t-test will be applied to each safety measurement after data normalization.

We define the analysis population as the enrolled participants who have successfully completed the trial. We will characterize the types of individuals who have missing data to better understand the nature the missing mechanisms. We will use statistical models to impute missing values if the assumption of missing at random is met. This can preserve and utilize the information of the non-missing values.

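### The abstract names mean PSQI change as the primary outcome, while the methods define, size and test a responder proportion at a 25% reduction

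*Protocol article*

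**What the plan says.** Abstract, Design: "The primary outcome measures will be the mean change in the Pittsburgh Sleep Quality Index (PSQI) from baseline" to the end of treatment. This is a comparison of means on a 0–21 score.

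Methods, Pittsburgh Sleep Quality Index: "The primary outcome is defined to have a value of 0 if RR is < 25% (ineffective) and 1 if RR is > 25"%. The next sentence reads: "The proportion of 1s (i.e. RR ≥ 25%) will be compared between the treatment and placebo groups". This is a comparison of two proportions.

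Sample size: success rates of 40% (placebo) and 70% (Jiao-tai-wan), 80% power, 49 evaluable per group raised to 62 for 20% drop-out; the total "at a two-sided alpha level of 5% is 124 participants". All inputs are responder rates.

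Statistical analysis: "For the primary outcome, we will use Fisher’s exact test", two-sided. Tests are then named for the polysomnography variables, adenosine and melatonin, GABA/Cr and the disharmony score. None is named for mean PSQI change.

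**The concern.** A difference in mean change and a difference in responder proportions answer different questions. The responder variable divides by the baseline score, so the same absolute improvement counts differently from person to person. A fall of 3 points is 3/7 = 43% for someone entering at the eligibility minimum of 7 (a responder), but 3/21 = 14% for someone at the top of the scale (a non-responder). Two analysts, one working from the abstract and one from the methods, could therefore reach different conclusions from the same data, and each could cite this document for having analysed the primary outcome. The abstract's version also has no test, effect size or SD behind it.

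**Working it through.** **1. Which sections agree**

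| Place | Primary variable | Comparison |
|---|---|---|
| Abstract, Design | change in PSQI score | means |
| Pittsburgh Sleep Quality Index | 0/1 at 25% reduction rate (RR) | proportions |
| Sample size | success, 40% vs 70% | proportions |
| Statistical analysis | not restated | Fisher's exact test |

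One sentence stands against three consistent sections.

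**2. The plan's own sample size**

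Inputs from Sample size: p₁ = 0.70, p₀ = 0.40, two-sided α = 0.05, power 0.80, mean proportion 0.55.

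- Two proportions, uncorrected: n′ = [1.960·√(2·0.55·0.45) + 0.842·√(0.70·0.30 + 0.40·0.60)]² / 0.30² = 41.97, so 42.
- With continuity correction: n = (n′/4)·[1 + √(1 + 4/(n′·0.30))]² = (41.97/4)·[1 + √1.318]² = 48.4, so 49.
- Drop-out: 49/(1 − 0.2) = 61.25, so 62 per group and 124 in total.

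The stated 49, 62 and 124 are reproduced. (The formula as printed, with α and β/2, gives (1.645 + 1.282)² × 110 × 45/900 = 47.1, so 48, which is close.) Enumerating all tables, two-sided Fisher's test has 81.5% power at 49 per group and 91.0% at 62. The responder version is adequately sized for its named test.

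**3. How often the two versions would disagree (illustrative)**

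The document gives no PSQI mean difference or SD, so an assumption is needed: a normal outcome with equal SDs, cut at the responder threshold. Then d = z(0.70) − z(0.40) = 0.524 + 0.253 = 0.778 SD. At 49 per group:

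| d | Fisher power (40% placebo) | t-test power | gap (points) |
|---|---|---|---|
| 0.5 | 43.5% | 68.8% | 25.3 |
| 0.6 | 58.9% | 83.6% | 24.7 |
| 0.7 | 72.8% | 92.9% | 20.1 |
| 0.778 | 81.5% | 96.8% | 15.3 |

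The gap is a lower bound on the rate of disagreement. Simulating 100,000 trials at d = 0.778, the tests disagreed on significance in 15.8%: t-test alone significant in 15.5%, Fisher alone in 0.3%. That is about one trial in six.

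**4. Type I error if either could be claimed (illustrative)**

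Under the null at 49 per group with 40% success in both arms, simulated rejection was about 5% for the t-test and 3% for Fisher. Rejection by either lay between 6.2% and 6.6% across runs, so about 6.4%.

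**5. Whether the responder definition can be applied as printed**

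The printed rate is RR = (score 1 − score 0)/score 0, with score 0 the baseline and higher scores worse.

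- Improvement from 12 to 6: (6 − 12)/12 = −50%. This is below 25%, hence ineffective as printed.
- Worsening from 8 to 12: (12 − 8)/8 = +50%, hence a success as printed.
- A reduction of exactly 25% (12 to 9, with the sign corrected) is neither below nor above 25% in the 0/1 definition, yet the following sentence counts it as a success.

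The intention is clear from the word reduction and from the category labels, but the literal text reverses it.

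**The case against.** The strongest reply is that the body governs. The methods, sample size and statistical analysis agree on one variable, one comparison and one two-sided test; the abstract sentence is loose wording. That stands, and it rules out a stronger claim that a reader might infer: that the confirmatory test is left open. What remains is a plain contradiction about the primary outcome in the part of the paper most people read, together with a body definition that itself needs repair.

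A reader might also infer that the trial is underpowered or has chosen a wrong endpoint because the score would give more power. The document does not support that. Dichotomising does lose information, but the trial was sized for the responder rate and its test meets the 80% target. The t-test figures rest on d = 0.778, obtained by cutting what is really a percentage change. Carrying that value over to raw mean change, or to a baseline-adjusted analysis, needs further assumptions about baseline spread and correlation.

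It is fair, too, that no section plans to test both outcomes and claim either, so the 6.4% describes a possible consequence of the ambiguity and not a planned procedure.

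Finally, a reader might set the start of recruitment (September 2018), registration (1 November 2018) and protocol version 1.3 (February 2020) side by side and suspect that the outcome was changed. Those dates do not show that. Neither the registry record nor any earlier protocol version is at hand.

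**Conclusion.** The contradiction holds: the abstract and the body name two different primary estimands, and only the body's has a test and a sample size. The body is internally consistent on endpoint type, sizing and test, so this is a defect of statement that can be reconciled and not an absent confirmatory plan or a power failure. If it is left as it is, the label primary could decide the conclusion in about 16% of trials at the design effect and 49 per group, and claiming either version would give a type I error of about 6.4% instead of 5%. Both figures assume a normal outcome with equal SDs. They indicate scale and are not estimates for this trial. The sign of RR and the treatment of exactly 25% are errors in the text itself and need no assumption.

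**What to change.** Before unblinding, state one primary outcome in the same words in the abstract, methods, sample size, statistical analysis and registry entry.

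- **Least disruptive choice:** keep the responder proportion with two-sided Fisher's exact test, since N = 124 rests on it, and rewrite the abstract sentence to match.
- **In the same edit:** define RR = (score 0 − score 1)/score 0 × 100%, and set the outcome to 1 if RR ≥ 25% and 0 otherwise, with the same boundary wherever it appears.
- **Add as first secondary:** end-of-treatment PSQI by ANCOVA with baseline PSQI as covariate, reported as a mean difference with 95% CI. This gives the abstract's quantity a planned analysis from data already collected.
- **Disclose** the date of the change relative to the start of recruitment.

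Making the continuous score primary is optional and carries a cost: it would change the primary after recruitment began, to an outcome for which the document gives no mean difference or SD.

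The recommended route costs wording changes and one extra model. It needs no change to the sample size and no new measurements.

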**Discussion:**

The outcomes of this study will confirm the efficacy of JTW for the treatment of insomnia symptoms and will also be used to monitor the safety of JTW.

**Trial registration:**

Chinese Clinical Trial Registry, ChiCTR1800019239. Registered on 1st November 2018.

## Background

Sleep is essential to human health, but unfortunately, nearly one-third to one-quarter of the population in resource-poor countries suffer from insomnia at some level [1, 2]. With the increasing incidence of insomnia, there are different degrees of depression, anxiety, and other psychological diseases, which seriously affect the quality of a person’s daily life [3]. Psychological and behavioral therapy, Western medicinal therapy, and traditional medicinal therapy are the main treatments for insomnia [4]. Many clinical studies have supported the first two treatments; however, some risks of adverse reactions and tolerance have been reported. In addition, dependence and addiction seriously impact clinical efficacy. For instance, the long-term use of zolpidem, which is relatively safe and frequently prescribed for the treatment of transient insomnia, will increase the risk of dementia [5]. Thus, interest in using traditional medicinal therapies is increasing, especially in traditional herbal medicine [6].

The superiority and soul of traditional East Asian medicine is the system called “pattern identification,” which is used to diagnose and treat diseases based on the symptoms and the signs observed in patients. According to this system, insomnia has many different patterns, but disharmony of the heart and kidney is the dominant pattern [7, 8]. Moreover, Jiao-tai-wan (JTW) has been commonly used for the management of insomnia with a disharmony of heart and kidney pattern for centuries in China, Korea, and Japan [9].

In a review article by Yeung et al. [10], JTW was listed as one of the 10 most frequently examined standardized traditional herbal formulas for insomnia. A clinical study conducted in China showed that administration of JTW for 60 consecutive days could improve the Pittsburgh Sleep Quality Index (PSQI) [11]. Lu et al. [12] reported a significant decrease in scores in the Disharmony of Heart and Kidney Scoring System. Another study [13] demonstrated the effects of JTW in detail by alleviating the symptoms of palpitation and dizziness caused by the disharmony of the heart and kidney.

Although recent clinical studies have shown the efficacy of JTW in the treatment of insomnia, a randomized, double-blind, placebo-controlled pilot clinical trial to confirm its efficacy has not yet been undertaken. We set up this study to better clarify the efficacy, safety, and feasibility of JTW for treating insomnia caused by disharmony of the heart and kidney and to provide data for evidence-based clinical practice.

## Methods and design

### Study design

This is a parallel group randomized superiority clinical trial comparing JTW to placebo for efficacy in treating insomnia. The choice of using a placebo for the trial in order to test the rationality of the study design and to explore the effectiveness of JTW. Eligible participants will be randomly assigned to either the JTW or placebo group in an equal proportion. The drug intervention will last for 1 week. Figure 1 briefly shows the study flow chart and Fig. 2 enumerates the treatment schedule and outcome measures. The study adheres to the Standard Protocol Items: Recommendations for Interventional Trials (SPIRIT 2013) checklist [14] (Additional file 1).

**Fig. 1 Fig1:**
[figure not shown]
Flow chart of the study design

**Fig. 2 Fig2:**
[figure not shown]
SPIRIT schedule for enrollment, treatment, and assessments

### Participants

#### Study population

Patients suffering from insomnia symptoms caused by the disharmony of the heart and kidney will be recruited from the Traditional Chinese Medicine Department and Sleep Centre of the First Affiliated Hospital of Wenzhou Medical University in Wenzhou, Zhejiang Province, China. To recruit target participants, advertisements will be distributed using flyers, Wechat, and online and offline bulletin boards of the hospital.

#### Inclusion criteria

Participants are aged 18–60 years, either male or female, and with a level of education above junior high school.Insomnia is almost the only symptom, including difficulty sleeping, deep sleep, dreaminess, early-morning awakening, trouble going back to sleep, feeling tired after waking up, or daytime sleepiness (excluding secondary insomnia).A PSQI score of 7 or higher according to the Chinese Classification and Diagnostic Criteria of Mental Disorders-3 Version, CCMD-3 [15].A Disharmony of Heart and Kidney Scoring System score of 9 or higher.Signed informed consent before treatment.

#### Exclusion criteria

Insomnia caused by physical diseases or lifestyle changes or environmental disturbances.Affective disorders, anxiety disorder, depression, schizophrenia, and any other serious mental disorders.Suffering from somatic diseases that affect the central nervous systemSerious heart, liver, kidney, and hematopoietic system diseases, abnormal liver and kidney function.Regular use of antipsychotic drugs in the last month.Use of medicine to treatment sleeping disorders in the past week.Allergic to a certain ingredient of the drug involved in this trial or suffering from allergies.Alcohol abuse and/or psychotropic drug addiction.Pregnancy or lactation.

### Randomization and allocation concealment

We will apply block randomization to generate a sequence of labels (A or B) at 1:1 ratio, numbered from 001 to 124. This randomization approach forces balance between treatment and placebo groups over time as the recruitment proceeds. The pharmaceutical company will prepare the trial intervention packages according to the labeled sequence (A or B), numbered from 001 to 124, all in uniform plastic packages. The study coordinator will be blinded to the group assignment and will give participants the numbered package of intervention according to their visiting time sequence at baseline visit (e.g. the first participant will get the package numbered 001, the second participant will get packaged 002, and so on). Thus, the allocation concealment will be maintained throughout the study. The generated sequence of the group assignment and numbers will be sealed in opaque envelopes and stored in double-locked cabinets. Allocation concealment will be maintained throughout the entire study.

### Blinding

The present study will use a double-blind method. The placebos and JTW will look the same and will be packaged in uniform plastic bags. Then, the study coordinator will assign JTW or placebo according to the randomization codes and place them in special containers. The participants, outcome assessors, study coordinators, data managers, and statisticians will be blinded to the group allocation and numbered drug containers throughout the entire study. At the end of the study, the blinding codes will be revealed.

If unblinding is required, the trial managers and data coordinators will have access to group allocations and any unblinding will be reported.

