### Intervention

These eligible participants will ingest 2 g granules of JTW or placebo, twice a day at 1600 hours and 2100 hours for 1 week and present themselves at the termination of medication, followed by a scheduled examination.

Both JTW and placebo are manufactured by the Kangren Pharmaceutical Factory according to good manufacturing practice standards. JTW will be produced in the form of granules with a yellowish-brown color. The medication will be 2 g, containing 1.1 g JTW soft extract with 0.37 g of lactose hydrate and 0.88 g of corn starch as the excipient. The JTW soft extract will be made of a water extract of a mixture of two herbal medicines, as follows: Rhizome Coptidis (10 g) and Cortex Cinnamomi (1 g). The placebo will consist of corn starch, lactose hydrate, citric acid, and caramel color. The placebo and JTW will have the same appearance and color.

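### The protocol gives two incompatible accounts of who links the randomisation code to the product, and one of them would unblind the study coordinator who dispenses it

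*Protocol article*

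**What the plan says.** Two neighbouring sections of the protocol article describe how product reaches the participant.

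Under Randomization and allocation concealment, the work is done off site: "The pharmaceutical company will prepare the trial intervention packages according to the labeled sequence (A or B), numbered from 001 to 124". The coordinator's part is limited: "The study coordinator will be blinded to the group assignment and will give participants the numbered package of intervention according to their visiting time sequence". The sequence itself is kept under seal in locked storage.

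Under Blinding, the products are first made to look alike and put in uniform bags. After that, "the study coordinator will assign JTW or placebo according to the randomization codes and place them in special containers". The next sentence reads: "The participants, outcome assessors, study coordinators, data managers, and statisticians will be blinded to the group allocation and numbered drug containers throughout the entire study". The section closes with a code-break provision. If unblinding is needed, trial managers and data coordinators get access to allocations, and any such event is reported.

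**The concern.** The first account is a sound numbered-kit design. The manufacturer ties product to number, the list is locked away, and the person at the clinic knows only which number comes next. The second account has that same person sort active product and placebo by code. Someone who does that knows what is in each container, and so cannot also be blinded.

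Two protections are at stake. The first is allocation concealment. Packages go out in order of visit, so a dispenser who holds the code knows the next assignment before the next participant receives it. The second is the double-blind. The PSQI is a self-reported questionnaire, and the primary outcome is built from it. Researchers judge how adverse events relate to the study drug. Non-compliance is a ground for drop-out, and drop-outs are left out of the final analysis. Knowledge of allocation among site staff could therefore reach the scores, the safety judgements and the choice of who is analysed.

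**Working it through.** The plan attaches no figure to this point, so the check is a comparison of the text.

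1. **Who ties code to product?** Randomization section: the pharmaceutical company, when it packs to the sequence. Blinding section: the study coordinator, after bagging. These are different parties at different stages.

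2. **What is left for the coordinator to assign?** Under the Randomization section, nothing. Each package 001 to 124 already has its content fixed, and the participant's place in the visit order fixes the number. A further step in which the coordinator assigns active product or placebo has no place in that procedure.

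3. **Can the coordinator work from the code at all?** The Randomization section keeps the sequence sealed and locked, and says "The study coordinator will be blinded to the group assignment". The Blinding section has the coordinator act on the randomisation codes. Both can be true only if *codes* means something that does not reveal treatment.

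4. **Does the Blinding section agree with itself?** One sentence has the coordinator place product in containers by code. The next blinds study coordinators to the allocation and to the numbered containers. Read literally, the person who fills the containers is blinded to them.

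5. **Try the mildest reading.** Let *codes* mean package numbers only. The coordinator then moves identical-looking numbered bags into containers and learns nothing, so steps 3 and 4 largely resolve. Steps 1 and 2 do not. The sentence names the two treatments, not the package numbers, as what the coordinator assigns, and the company has already made that link. Two accounts remain, and site staff could follow either one.

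6. **Consequence of the literal reading.** The role that hands out product in visit order would know every assignment it hands out. Concealment and blinding then both fail for that role.

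The contradiction does not depend on the success rates, the sample size or any other numerical assumption.

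**The case against.** The best defence is that one sentence is loosely worded and the intent is clear. The bags already look alike when the coordinator acts, the sequence is sealed, and both sections say that the coordinator is blinded. If *codes* means package numbers, nothing leaks. The route to harm is also indirect: participants, who complete the PSQI, are stated to be blinded, and adverse events are judged by researchers who are not said to be the coordinator. All of this stands as a reason not to claim that blinding has been broken. It does not remove the need to correct the text, because the sentence names the treatments and assigns to site staff a step that the other section gives to the manufacturer.

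A reader might infer more, and the document does not support it:

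- *That data coordinators have standing access to allocations.* The statement that "the trial managers and data coordinators will have access to group allocations" is conditional on unblinding being required, and any unblinding is reported. It is a code-break provision and does not contradict double-blinding. The blinded list names data managers and study coordinators, not data coordinators or trial managers, so no role is stated to be both blinded and unblinded. What remains is a small ambiguity about whether data coordinators are a separate role.
- *That a two-letter code lets one unblinding expose all 124 participants.* This would need the A or B label to be visible on kits, forms or data. The document says only that packing follows a sequence of such labels; dispensing is by number.
- *That the placebo is distinguishable by taste or smell.* The document says "The placebo and JTW will have the same appearance and color" and is silent on taste and smell. Silence in a condensed article is not evidence of a mismatch. For the same reason, an added treatment-guess question would be a preference and would not repair this contradiction.

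**Conclusion.** The contradiction is real and lies in the stated text. The two sections disagree on who links code to product, and the Blinding section, read literally, also disagrees with its own next sentence. If its procedure were followed as written, the dispenser would know the allocation, and concealment and the double-blind would both be lost at that point.

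The effect on the results cannot be calculated from the document. That all 124 assignments pass through the coordinator is no measure of harm, since the same is true of the sound numbered-kit procedure. The conclusion rests on taking the words as written. On the mildest reading the breach disappears, but two incompatible descriptions of the same step remain. The text should be corrected; it is not evidence that any participant has been unblinded.

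**What to change.** In the Blinding section, delete the sentence that has the coordinator assign product by code. Keep the procedure in the Randomization section: the manufacturer packs and numbers to the sequence, and the coordinator only dispenses the next numbered kit, with no access to the codes. Add that the code list is held by a role with no part in dispensing, assessment or data handling.

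State whether data coordinators are distinct from the blinded data managers and study coordinators. The conditional unblinding provision needs no other change.

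The Trial status section says that recruitment began in September 2018, under a protocol now at version 1.3. Rewording alone will not settle what was done for participants already enrolled. Record which procedure has been used and since when, and report it with the results. If the coordinator did work from a code that revealed treatment, say so.

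The cost is a few sentences, a file note and, if needed, moving the code list to a different holder. Sample size, outcomes and analysis are unaffected.
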